# ECHITAB STUDY GROUP NIGERIA PROTOCOL

**Phase II/III randomised-blinded-comparative-non-inferiority trial of two antivenoms for the treatment of patients envenomed by saw-scaled vipers (*Echis ocellatus*) in Kaltungo, Nigeria.**

## INTRODUCTION

Snake bite is a major medical problem in rural communities of the savanna region of West Africa, notably in Nigeria, Senegal (Trape et al., 2001), Ghana, Benin, Togo, Burkina Faso, Niger, Mali and Cameroon. Saw-­scaled vipers *(Echis ocellatus* and *E. leucogaster*) are the most important cause of snake bite mortality and morbidity in this region followed by spitting cobras (*Naja nigricollis* and *N. katiensis*) and puff adders (*Bitis arietans*). Children, farmers, herdsmen and hunters are at the greatest risk. The main clinical features of *E. ocellatus* envenoming are systemic haemorrhage, incoagulable blood, shock and local necrosis. In Nigeria, where the untreated case fatality is 10-20 per cent, this species is responsible for hundreds of deaths each year (Warrell and Arnett, 1975; Warrell *et al* 1977; Pugh and Theakston 1980; 1987; Pugh *et al* 1979). In some rural hospitals, half of the beds are occupied by snake bite victims during the peak season (e.g. during the early rainy season when farmers prepare their land for planting between May and July, and later during the harvesting period). Medical management of snake bite is extremely difficult in this area. There is a general lack of reliable data and victims of snake bite are increasingly reluctant to seek medical assistance because of the perennial shortage and expense of antivenom. The rising cost and lack of availability of antivenom in recent years has put treatment out of the reach of most patients (Theakston and Warrell, 2002; Lalloo *et al*, 2002; Laing *et al*, 2003; Theakston et al., 2003). For example, antivenom of doubtful potency may cost Naira 3,000 – 4,000 per vial from local pharmacies. As a result, useless and potentially dangerous remedies such as the black 'snake stone' have gained in popularity. Over the past ten years, this shortage of antivenom has become so dire that, at the moment, there is virtually no antivenom available in the country because traditional suppliers such as South African Vaccine Producers and Sanofi-Pasteur are unable to fulfil orders from state governments such as Gombe. As a result, increasing numbers of patients bleed to death or survive with amputated extremities.

Antivenoms previously available in Nigeria have included the South African Vaccine Producers (formerly SAIMR) and Institut Pasteur monospecific Echis antivenoms, Behringwerke and Pasteur (Bitis-Echis-Naja) polyspecific antivenoms, Pasteur Ipser Afrique, (Bitis-Echis-Naja-Dendroaspis) polyspecific antivenom and ovine monospecific *Echis ocellatus* EchiTAb (Therapeutic Antibodies Ltd [TAb] and MicroPharm Ltd). For many reasons most of these preparations are no longer available (e.g. political, cost, difficulties in production etc). More recently, a new polyspecific antivenom, FAV-Afrique (Bites, Echis, Naja, Dendroaspis) produced by Sanofi-Pasteur, has become available although supplies are extremely limited; its cost in Africa may exceed £70 (~Naira 17,500) per ampoule. Recent information from the manufacturers is that no further capital investment will be made in its production and that continuing supply is assured for only 3-5 years.

Two caprylic acid-extracted whole IgG equine antivenoms with activity against *E. ocellatus* venom have been developed by the Instituto Clodomiro Picado (Costa Rica) (EchiTAb-Plus-ICP –“ET-Plus”) and MicroPharm (London) (EchiTAb-G – “ET-G”) in collaboration with the Liverpool School of Tropical Medicine and the University of Oxford. The Costa Rican antivenom was prepared by immunising with *E. ocellatus*, *Bitis arietans* and *Naja nigricollis* venoms, selected because these are the three most important species, from a medical point of view, in sub-Saharan Africa. The MicroPharm antivenom is monospecific against *E. ocellatus* venom that has been the standard of care for *E. ocellatus* envenoming in Nigeria since 2005. Preclinical tests using WHO-approved methods showed these antivenoms to be as effective or almost as effective against *E. ocellatus* venom as the original ovine Fab fragment monospecific “EchiTAb” (Meyer et al., 1997) in doses of 3 vials (ET-Plus) and 1 vial (ET-G).

In Kaltungo Hospital, an open preliminary dose-finding and safety study in a small group of envenomed patients confirmed that these doses “cured” 3-4/6 patients while causing reactions in 0-2/6. (A third antivenom was rejected because it was too reactogenic at a dose high enough to fulfil efficacy criteria). (“Cured” meant that the patient’s blood coagulability was permanently restored 6 hours after treatment, as judged by the 20-minute whole blood clotting test). These two antivenoms will be compared in a non-inferiority RCT.

## AIMS OF THE STUDY

*Echis ocellatus* Phase II/III randomised-comparative-trial (**PII/III R-C-T**): to assess and compare the efficacy and safety (incidence and severity of acute anaphylactic reactions) of a ET-Plus, a new antivenom, with ET-G, an antivenom of established efficacy. Both antivenoms achieved adequate efficacy and safety in an open preliminary dose-finding and safety study.

## SITE OF THE STUDIES

Kaltungo General Hospital, Gombe State in Nigeria has provided an ideal setting for several previous studies of Echis bite (1972-1994) (Warrell *et al*, 1974, 1980; Daudu and Theakston, 1988; Meyer *et al*, 1997). In 1982 there were 360 admissions for snakebite with 17 deaths and in 1985 there were almost 300 bites between January and May with 76 in April alone. From January 1983 to December 1986 a total of 1578 patients were admitted to the hospital giving a mean annual admission rate of 394.5. During this period there were 59 deaths, an average of 25 deaths per year ([name], personal communication). More recent data (1999-2004) indicate that the incidence of snake bite, primarily due to *E. ocellatus*, is undiminished. Morbidity and mortality may be increasing as a result of the crisis in antivenom production and supply to Africa (Theakston and Warrell, 2000).

## TIME AND DURATION

Starting in June 2005 and continuing until ~400 patients have been studied (see power calculations below).

## DESIGN

**PII/III R-C-T**

Randomised, comparative, blinded study of 2 antivenoms using as the initial dose the minimum effective safe dose established in the **PI** **D-FS (preliminary Phase I dose-finding and safety study).**

***Primary end-points***

Proportion of patients given each antivenom whose blood coagulability has been permanently restored 6 hr after the first dose.

***Sample size***

The trial is designed to demonstrate non-inferiority of ET-Plus compared to ET-G. Based on pre-trial clinical use of ET-G (released for human use on humanitarian grounds because of the lack of any other available antivenom) it was estimated that permanent restoration of blood coagulability at 6 hours would be achieved in 80% of patients in the ET-G group. A 10% non-inferiority margin was deemed acceptable (i.e. at least 70% of ET-Plus patients must have permanent restoration of blood coagulability at 6 hours for it to be deemed non-inferior to ET-G). A sample size of 198 in each group provides 80% power to detect this non-inferiority margin difference of 10%, at a 5% one-sided significance level.

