***Statistical methods***

Baseline characteristics will be described using percentages for categorical variables, means and standard deviations for normally distributed continuous variables or medians and ranges in the case of non-normally distributed continuous variables.

To determine the magnitude and direction of the treatment effects, relative risks and one-sided 95% confidence intervals will be calculated. Continuous outcomes will be checked for normality and the treatment groups will be compared using either the *t* test (for normally distributed data) or the Mann Whitney-U test (for non-normally distributed data). Treatment effects will be presented as a corresponding difference in means or medians (plus one-sided 95% confidence intervals).

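### The non-inferiority criterion is written as a fixed 70% success rate on ET-Plus alone, which matches the 10-point margin only if ET-G is exactly 80%, and the planned relative-risk interval is never tied to the margin

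*Protocol*

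**What the plan says.** The Sample size section gives the objective: "The trial is designed to demonstrate non-inferiority of ET-Plus compared to ET-G". It assumes that "permanent restoration of blood coagulability at 6 hours would be achieved in 80% of patients in the ET-G group", an estimate from clinical use before the trial. It then states that "A 10% non-inferiority margin was deemed acceptable" and explains this in a parenthesis opening with i.e.: "at least 70% of ET-Plus patients must have permanent restoration of blood coagulability at 6 hours for it to be deemed non-inferior". The section closes with the size: "A sample size of 198 in each group provides 80% power", for a 10% difference at a one-sided 5% level.

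The primary endpoint compares two arms: "Proportion of patients given each antivenom whose blood coagulability has been permanently restored 6 hr after the first dose".

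For treatment effects, the Statistical methods section says that "relative risks and one-sided 95% confidence intervals will be calculated". It does not mention the margin, and it plans differences only for continuous outcomes, as differences in means or medians.

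**The concern.** The parenthesis is the only sentence in the protocol that says what makes ET-Plus non-inferior, and it is a condition on one arm. It equals the margin only when ET-G is exactly 80%. If ET-G does better, an ET-Plus rate of 70% is more than 10 points worse and still meets the wording. If ET-G does worse, a product just as good as ET-G can miss it. The wording also does not say whether 70% is an observed proportion, a true rate or a confidence limit.

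A concurrent control is randomised because the control rate is uncertain. Here the 80% is a pre-trial estimate, and the Introduction reports that 3-4 of 6 patients were cured at these doses in the preliminary study. Those numbers are too small to contradict 80%, but they do not confirm it either. The primary conclusion of the trial depends on this sentence.

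**Working it through.** **Inputs.** ET-G rate 80%, margin 10 points, one-sided alpha 5%, power 80%, 198 per arm (all from Sample size). Both arms are taken as truly 80% for the power calculation. The section does not spell this out, but it is the assumption under which the figure reproduces.

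**Step 1: reproduce 198.** For a two-arm non-inferiority test on the difference with unpooled variance,

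n = (z0.95 + z0.80)² × [p1(1 - p1) + p2(1 - p2)] / margin²

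= (1.645 + 0.842)² × (0.16 + 0.16) / 0.10² = 6.183 × 0.32 / 0.01 = 197.8, so 198 per arm.

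Power at 198: SE = √(0.32/198) = 0.0402; 0.10/0.0402 - 1.645 = 0.843; power 80.0%. Other readings do not fit: one-sided 2.5% gives 252, and a one-sided superiority test of 80% against 70% gives 231 (251 with continuity correction). The trial was therefore sized for the rule that the lower one-sided 95% limit of the difference (ET-Plus minus ET-G) lies above -10 points.

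**Step 2: turn the parenthesis into a rule.** If 70% is an observed proportion, 0.70 × 198 = 138.6, so at least 139/198 (70.2%) is needed. The chance of passing is P(X ≥ 139) for X binomial with n = 198 and the true ET-Plus rate. The limit rule uses the Wald lower limit, enumerated exactly over both arms.

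**Step 3: ET-Plus truly 10 points worse (every pass is a false positive).**

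| True ET-G / ET-Plus | 70% wording alone | Limit rule | Both required |
|---|---|---|---|
| 70% / 60% | 0.2% | 5.1% | 0.2% |
| 75% / 65% | 7.1% | 5.0% | 2.8% |
| 78% / 68% | 28.0% | 5.1% | 4.7% |
| 80% / 70% | 51.0% | 5.0% | 4.95% |
| 85% / 75% | 94.7% | 5.0% | 5.0% |
| 90% / 80% | 99.96% | 5.3% | 5.3% |

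With ET-Plus 15 points worse (90% / 75%), the 70% wording alone passes 94.7% of the time and the limit rule 0.15%.

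**Step 4: identical products (a pass is correct).**

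| Both arms truly | 70% wording alone | Limit rule | Both required |
|---|---|---|---|
| 80% | 99.96% | 80.0% | 80.0% |
| 70% | 51.0% | 70.1% | 47.2% |
| 65% | 7.1% | 67.5% | 7.1% |

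**Step 5: one possible data set.** Suppose ET-G is 158/198 (79.8%) and ET-Plus 139/198 (70.2%). The 70% wording is met. The difference is -9.6 points, SE = √(0.702 × 0.298/198 + 0.798 × 0.202/198) = 0.0433, and the lower limit is -9.6 - 1.645 × 4.33 = -16.7 points, so the limit rule fails. ET-Plus would need at least 152/198 (76.8%).

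**Step 6: the scales.** At 80%, a 10-point margin corresponds to a ratio of 70/80 = 0.875. At 65% it is 55/65 = 0.846, and at 90% it is 80/90 = 0.889. A relative-risk interval cannot be set against the margin until a ratio margin is fixed, and the protocol fixes none.

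**The case against.** The best defence is that the parenthesis only illustrates the margin. It follows directly on the 80% assumption, and 80 minus 10 is 70. It is worded as something ET-Plus must satisfy, hence as necessary and not sufficient, and it may refer to the true rate, as margins often do in sample-size text. The same section sets a one-sided 5% level and calls the margin a difference. The analysis section plans between-arm intervals at the matching level, and 198 fits a two-arm test exactly. Details of the decision rule are also commonly left to the SAP, which is not shown.

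Much of this stands. A reader might infer that the trial has given up its control arm and its 5% error, or that the false-positive rate is always about 50% or more. The documents do not support either. The first conflicts with the sample size, the significance level and the planned between-arm comparison. The second holds only if ET-G is truly about 80% or higher; at 78% the figure is 28%, at 75% it is 7%. Added to a limit rule as a necessary condition, the 70% does not inflate type I error at all.

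The wording is still not harmless. The protocol writes no limit rule to which the 70% could be added, and even as an added condition it rejects equivalent products when ET-G falls short of 80%. Nor is this a complaint about missing detail: the sentence is present and is phrased as a criterion. An SAP with the usual rule would have to be reconciled with it.

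**Conclusion.** Wrong as written. A two-arm test was probably intended, but the stated criterion does not express it and does not deliver the stated one-sided 5% error. Taken as sufficient, its error for a product 10 points worse is uncontrolled, running from 7% (ET-G 75%) through 51% (ET-G at the planning rate of 80%) to 95% (ET-G 85%). Taken as an extra necessary condition, the harm is lost power: for identical products, from 70% to 47% if both are at 70%, and from 68% to 7% if both are at 65%. The relative-risk interval does not settle the matter, because it is on another scale from the margin.

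These figures assume 198 analysed per arm, 70% read as an observed proportion, and a Wald limit for the difference. The rates other than 80% are assumptions chosen to show the range; the protocol does not predict them.

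**What to change.** In Sample size, replace the parenthesis with: non-inferiority is concluded if the lower one-sided 95% confidence limit for the difference in success proportion (ET-Plus minus ET-G) lies above -10 percentage points. Keep 70% only as an illustration of what the margin means if ET-G is 80%.

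In Statistical methods, name the risk difference with its one-sided 95% interval as the primary analysis of the 6-hour endpoint, with the relative risk as supportive. If an SAP exists, check that it states the same rule.

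The cost is a wording change in two sections, to be made before unblinding. No patients are added: with 198 per arm the limit rule has 80.0% power at 80%/80% and a type I error of 5.0% at 80%/70%.

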***Randomisation***

Patients will be allocated to receive either ET-Plus or ET-G using simple randomisation, employing a table of random numbers. Treatment allocations will be concealed in sequentially numbered opaque sealed envelopes given to the hospital pharmacist who is otherwise independent of the study. He will provide the blinded antivenoms after reconstituting them to 40mls with sterile water for injection in an unmarked syringe. The patient, clinician and outcome assessor will be blinded to the identity of the particular antivenom used.

***Statistical methods***

Baseline characteristics will be described using percentages for categorical variables, means and standard deviations for normally distributed continuous variables or medians and ranges in the case of non-normally distributed continuous variables.

To determine the magnitude and direction of the treatment effects, relative risks and one-sided 95% confidence intervals will be calculated. Continuous outcomes will be checked for normality and the treatment groups will be compared using either the *t* test (for normally distributed data) or the Mann Whitney-U test (for non-normally distributed data). Treatment effects will be presented as a corresponding difference in means or medians (plus one-sided 95% confidence intervals).

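### The non-inferiority margin and the 198 per group are set on the risk-difference scale, but the only effect measure named for binary outcomes is the relative risk, which has no margin

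*Protocol*

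**What the plan says.** The primary endpoint (Protocol, Primary end-points) is binary: "Proportion of patients given each antivenom whose blood coagulability has been permanently restored 6 hr after the first dose".

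The Sample size section states the aim, "The trial is designed to demonstrate non-inferiority of ET-Plus compared to ET-G", and plans on the expectation that "permanent restoration of blood coagulability at 6 hours would be achieved in 80% of patients in the ET-G group". It gives the margin as two percentages: "A 10% non-inferiority margin was deemed acceptable (i.e. at least 70% of ET-Plus patients must have permanent restoration of blood coagulability at 6 hours". It then says: "A sample size of 198 in each group provides 80% power to detect this non-inferiority margin difference of 10%, at a 5% one-sided significance level".

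The Statistical methods section turns to treatment effects with: "To determine the magnitude and direction of the treatment effects, relative risks and one-sided 95% confidence intervals will be calculated". Differences appear only afterwards, for the means or medians of continuous outcomes. The section names no risk difference for a binary outcome, gives no relative-risk margin, and has no sentence that connects an interval with the 10 points.

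**The concern.** A non-inferiority conclusion comes from placing a confidence limit against a margin, so the two must be on the same scale. Here the margin is a difference between two percentages and the planned interval is for their ratio. A fixed difference corresponds to a different ratio at each control success rate, so no single relative risk stands in for 10 points.

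This goes beyond detail left for a later document. The protocol does name an effect measure, and it is not the one on which it set its margin and sample size. If the relative risk is used for the decision, someone has to convert the margin, possibly once the ET-G rate is known. The conversion can change the conclusion and the rate of false claims of non-inferiority.

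The 80% for ET-G is an estimate from clinical use before the trial. The Introduction reports cure in 3-4 of 6 patients at the trial doses. Those numbers are far too small to replace 80%, but they show that the rate was not firmly known.

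**Working it through.** **Inputs.** From Sample size: ET-G success 80%, margin 10 points, one-sided 5%, power 80%, 198 per group. From Statistical methods: relative risk with a one-sided 95% interval. My assumptions: Wald limits on each scale, equal arms of 198, and ET-G rates of 60% to 90% to show the range.

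**1. The protocol's own figure.** On the risk-difference scale with no true difference:

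n = (1.645 + 0.842)² × 2 × 0.8 × 0.2 / 0.10² = 197.84, rounded up to 198.

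This matches exactly. Power at 198: SE = √(0.32/198) = 0.0402; 0.10/0.0402 = 2.487; Φ(2.487 − 1.645) = 80.0%. Exact binomial enumeration also gives 80.0%. The stated 80% is therefore the power of a risk-difference analysis.

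**2. The relative-risk test implied by the planning figures.** The margin is 0.70/0.80 = 0.875. At 80% in both arms, SE of log RR = √(2 × 0.2/(0.8 × 198)) = 0.0503; ln 0.875 = −0.1335; 0.1335/0.0503 = 2.657; power = Φ(2.657 − 1.645) = 84.4% (exact 84.2%).

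**3. How the scales separate.** Ten points at control rate p equals RR (p − 0.10)/p. A fixed RR of 0.875 tolerates a loss of 0.125p. The last two columns give the probability, by exact enumeration with 198 per arm, of declaring non-inferiority when ET-Plus is truly 10 points worse.

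| ET-G success | RR equal to 10 points | Loss tolerated by RR 0.875 | False claim, RR 0.875 | False claim, risk difference |
|---|---|---|---|---|
| 60% | 0.833 | 7.5 points | 1.5% | 4.9% |
| 70% | 0.857 | 8.75 points | 2.8% | 5.1% |
| 80% | 0.875 | 10 points | 5.2% | 5.0% |
| 90% | 0.889 | 11.25 points | 11.1% | 5.3% |

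**4. Single datasets on which the two tests disagree** (one-sided 95% lower limits):

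- ET-G 178/198, ET-Plus 167/198. Difference −5.6 points, SE 3.35, lower limit −5.56 − 1.645 × 3.35 = −11.1 points: fails. RR 0.938, lower limit 0.880: passes 0.875.
- ET-G 119/198, ET-Plus 117/198. Difference −1.0 point, SE 4.93, lower limit −1.01 − 1.645 × 4.93 = −9.1 points: passes. RR 0.983, lower limit 0.858: fails 0.875.

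**The case against.** The strongest reply is that Statistical methods describes estimation, the size and direction of effects, and is not labelled as the non-inferiority test. It covers other binary outcomes too, such as reactions. It does not forbid subtracting the two proportions and applying the one margin the protocol gives, and a statistical analysis plan that is not shown may say exactly that. At the planned 80% the two boundaries coincide, and the one-sided 95% interval agrees with the one-sided 5% level. All of this stands. A reader might infer that the trial cannot test its hypothesis, and the text does not support that. What remains is that the protocol does name a measure for binary outcomes, and it is on a different scale from its margin.

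A reader might also infer that the trial lacks its stated 80% power. That does not follow either. The only relative-risk margin derivable from the protocol, 0.875, gives about 84%. Two other margins give less, but neither fits the text:

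- RR 0.90 gives 67%, but it reads the 10% as relative and contradicts the protocol's own gloss of at least 70% success on ET-Plus.
- The relative risk of failure against 30/20 = 1.5 gives about 65%, but the primary endpoint fixes the event as restoration.

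At 60% success in both arms, power is lower on both scales (65% for the risk difference, 49% for RR 0.875). The protocol claims 80% power only at its planning rate, so this does not contradict it.

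**Conclusion.** The mismatch of scale holds. The margin and the 198 per group are absolute, the named measure is relative, and the protocol gives no conversion. The natural conversion, 0.875, keeps the intended error rate only near 80% ET-G success. With a true 10-point deficit, its false-claim rate runs from 1.5% at 60% to 11.1% at 90%, against 4.9% to 5.3% for the risk difference. These figures assume 198 per arm, Wald limits and a relative-risk margin fixed at 0.875.

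The sample size is correct for the risk difference, and no loss of power is shown under the planning assumptions. On the relative-risk scale, power is undefined until a margin is stated. The point concerns the primary comparison and should be settled before the data are analysed.

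**What to change.** In Statistical methods, add two sentences:

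- The primary analysis is the risk difference (ET-Plus minus ET-G) in permanent restoration of coagulability at 6 hours, and non-inferiority is concluded if its one-sided 95% lower limit lies above −10 percentage points.
- The relative risk is reported as a supportive measure.

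The interval method should be named in advance, here or in the statistical analysis plan. The change needs no further patients or data. The sample size stays at 198 per group, and the stated 80% power then belongs to the analysis that is planned.

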## PATIENTS

All patients presenting to Kaltungo General Hospital, Gombe State, Nigeria (June 2005 owards) with a history of snake bite will be reviewed for possible recruitment into the study.

Inclusions: patients of both sexes and any age provided that:

1. they have incoagulable blood as defined by 20WBCT (diagnostic of systemic envenoming by *E. ocellatus* in this geographical area).
2. they have been bitten within the previous 72 hours
3. they or their relatives have given informed consent to admission, treatment and investigation

Exclusions:

1. patients who have already received antivenom for this (recent) snake bite
2. pregnant women
3. patients who are unconscious and/or have lateralising neurological signs indicative of established intracerebral haemorrhage
4. patients with a severe unrelated medical condition such as advanced AIDS or tuberculosis

Patients will be admitted to hospital and kept under observation for at least 48 hours after their blood has become coagulable because of the risk of late recurrence of incoagulable blood and bleeding.

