**Local signs:**

• Extent of local swelling (and usually of tenderness):

| **score** | Description |
| --- | --- |
| **1** | Confined to the bitten segment of limb |
| **2** | Extension to mid fore-arm of mid-calf |
| **3** | To knee or elbow |
| **4** | To mid-upper arm or thigh |
| **5** | To shoulder or inguinal ligament |
| **6** | Spreading to trunk |

• Bleeding from fang marks or local incisions

• Blistering

• Bruising

• Necrosis

• Tender, enlarged, painful lymph nodes draining the bitten area

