**Systemic signs:**

• Spontaneous systemic bleeding (from gums, nose, skin, gastrointestinal or genitourinary tracts, urine etc)

• Incoagulable blood (20WBCT)

• Shock (supine systolic blood pressure less than 80 mm Hg with impaired peripheral circulation)

• Cardiac arrhythmias

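### Free improvement, not an error: the 6-hour comparison could be adjusted for baseline factors the trial already records, although the crude analysis is valid as it stands

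*Protocol*

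**What the plan says.** The primary endpoint (Protocol, Primary end-points) is binary: "Proportion of patients given each antivenom whose blood coagulability has been permanently restored 6 hr after the first dose".

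The Sample size section assumes that "permanent restoration of blood coagulability at 6 hours would be achieved in 80% of patients in the ET-G group". It sets the margin on the absolute scale: "A 10% non-inferiority margin was deemed acceptable (i.e. at least 70% of ET-Plus patients must have permanent restoration". It arrives at 198 per arm for 80% power at one-sided 5%.

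Patients are allocated "using simple randomisation, employing a table of random numbers", and no strata or blocks are mentioned. Eligibility is broad: any age, provided that "they have been bitten within the previous 72 hours".

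Statistical methods gives baseline characteristics a descriptive role. For the treatment effect, "relative risks and one-sided 95% confidence intervals will be calculated". Continuous outcomes get a *t* test or a Mann-Whitney test. All of these are two-group methods as described, and no covariate is named.

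The Methods section has history and examination recorded on admission, including the extent of swelling on a 1 to 6 score (Local signs) and spontaneous systemic bleeding (Systemic signs). The proforma in Annexe 1 has fields for age, weight, date and time of bite, date and time of admission, and start time of each antivenom dose.

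**The concern.** Patients may arrive an hour or three days after the bite, at any age, with swelling limited to the bitten segment or reaching the trunk. If such factors predict whether clotting has returned at 6 hours, they add variation that a crude comparison leaves in the standard error. Simple randomisation can also leave them somewhat uneven between arms.

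Neither the allocation nor the stated comparison uses this information, although it is collected anyway. At stake is some precision on the primary question, and an estimate in the realised trial that may be shifted by chance imbalance that could have been corrected.

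**Working it through.** **1. The plan's own figure.** Inputs from Sample size: 80% in both arms (true difference taken as zero), margin 0.10, one-sided 5%, power 80%.

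- n per arm = 2 × 0.80 × 0.20 × (1.645 + 0.842)² / 0.10² = 197.8, so 198. This matches.
- Standard error at 198 per arm = √(0.32 / 198) = 0.0402. Power = Φ(0.10 / 0.0402 − 1.645) = 80.03%.
- Simple randomisation will not give exactly equal arms, but a 178/218 split still gives 79.7%.

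The stated power is therefore reached without adjustment.

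**2. Power with adjustment.** Let R² be the share of outcome variance explained by the baseline covariates. The protocol gives no value, so R² is an assumption. The variance of the difference is multiplied by (1 − R²):

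Power = Φ(0.10 / √((1 − R²) × 0.32 / 198) − 1.645)

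| Assumed R² | Standard error (points) | Power at 198 per arm | n per arm for 80% power |
| --- | --- | --- | --- |
| 0 | 4.02 | 80.0% | 198 |
| 0.02 | 3.98 | 80.7% | 194 |
| 0.05 | 3.92 | 81.8% | 188 |
| 0.10 | 3.81 | 83.6% | 179 |
| 0.20 | 3.60 | 87.2% | 159 |

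To give R² a scale: a factor present in half the patients that changes the success rate by 10, 20 or 30 points explains 0.25 × effect² / 0.16 = 1.6%, 6.3% or 14.1% of the variance.

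**3. Simulation.** 396 patients were simply randomised, with one normally distributed covariate and 4,000 trials per setting. The crude difference was compared with the logistic-standardised difference. Simulation error is about √(0.8 × 0.2 / 4000) = 0.6 points for power and √(0.05 × 0.95 / 4000) = 0.3 points for type I error.

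| R² | Power, crude | Power, adjusted | Type I error, crude | Type I error, adjusted |
| --- | --- | --- | --- | --- |
| 0 | 80.4% | 80.5% | 4.5% | 4.5% |
| about 0.04 | 80.2% | 81.3% | 5.3% | 5.2% |
| about 0.09 | 79.5% | 83.2% | 4.8% | 4.5% |
| about 0.18 | 79.4% | 86.2% | 5.0% | 5.1% |

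Type I error was simulated with true rates of 80% and 70%. Neither analysis inflates it, and adjusting for a useless covariate cost nothing measurable.

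**4. Chance imbalance.** For a factor present in half the patients, the standard deviation of the between-arm difference is √(0.25 × 2 / 198) = 5.03 points. The 95% range is ±1.96 × 5.03 = about ±9.85 points. If the factor changes the success rate by 10, 20 or 30 points (assumed), an imbalance at that limit moves the crude difference by about 1.0, 2.0 or 3.0 points. The standard error is 4.02 points and the margin is 10.

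**5. Is the model supportable?** At 80% success, 396 patients give about 0.20 × 396 = 79 failures. Treatment plus four covariates entered as single terms is five coefficients, or about 16 failures per coefficient.

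**The case against.** The strongest reply is that nothing in the protocol is wrong. The sample size reproduces, the error rate is held, and the confidence interval already allows for chance imbalance. That all stands. A reader might infer that the trial is underpowered for want of adjustment, or that simple randomisation leaves its result biased. The documents support neither: 80% power is reached unadjusted, and imbalance of this kind is random error already counted in the standard error.

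Second, covariate lists usually belong in a SAP, and one may exist unseen. The protocol does not use the word unadjusted or exclude adjusted estimates. This stands as a reason not to call the point an omission. It does not remove the suggestion, because the protocol states its comparison rather than leaving it open, and the stated comparison uses no baseline data.

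Third, the benefit is unknown. No document figure shows that age, delay, swelling or bleeding predicts the 6-hour result. Every patient enters with incoagulable blood, so the baseline value of the outcome test cannot serve as a covariate. This stands: the gain could be nil. It does not argue against adjusting, since the cost when R² is zero is negligible.

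Fourth, the covariates are imperfect. Bite time comes from history, and the proforma's local-symptoms table still carries a query over how extent is defined. Error recorded before treatment and unrelated to arm shrinks the gain but does not bias the comparison.

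Last, the margin is absolute while the planned measure is a relative risk. That is a separate matter of scale, and no part of the benefit claimed here comes from it.

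**Conclusion.** The point holds as an efficiency improvement at almost no cost. The crude analysis is valid and delivers its stated 80% power. Adjustment would add about 1 to 4 points of power if the recorded covariates explain 2% to 10% of outcome variance, about 7 points at 20%, and possibly nothing. It would also remove most of a 1 to 3 point conditional shift in the estimate, should a factor of the assumed strength be imbalanced near its 95% limit.

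These figures assume 80% success in both arms, 198 per arm and complete outcomes. The R² values and factor effects are assumptions, not protocol figures. The closeness of 396 to the planned total of about 400 concerns allowance for losses. It is a separate question and does not turn this point into a shortfall.

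**What to change.** Before unblinding, add one paragraph to the analysis plan:

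- **Covariates.** Fix a short list: age, hours from bite to first dose, swelling score (1 to 6) and spontaneous systemic bleeding (yes/no). If preparing the dose could take longer in one arm, hours from bite to admission is the strictly pre-randomisation version, and the proforma has both times.
- **Estimate.** Fit a logistic model with treatment and these covariates. Average the predicted probabilities over all patients under each antivenom, and compare the two standardised proportions with a robust or bootstrap one-sided 95% bound, judged against the 10-point margin. This keeps a marginal effect, which the margin needs. A conditional odds ratio would not match it.
- **Missing baseline values.** Use a simple rule, such as single imputation that ignores arm, so that no patient is dropped for lack of a covariate.
- **Sensitivity analysis.** Report the crude estimate alongside.

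The cost is the drafting and a slightly longer analysis program. No further patients or measurements are needed. The list must be fixed in advance, because covariates chosen after seeing results would be open to challenge.
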